**Figure 2 F2:**
[figure not shown]
Directed acyclic graph for investigating the effect of body composition changes on surgical outcomes. Baseline and preoperative well-being include nutritional status, psychological well-being and physical fitness.

Pearson (or Spearman, depending on the distribution of the data) correlation coefficients will be calculated to explore associations between outcome measures (eg, body weight, size and shape, body composition, body mass change, PG-SGA-SF, EQ-5D-5L, etc) and clinical outcomes (eg, surgical complications, length of stay, number of emergency readmissions and length of operating time). P values <0.05 will be considered statistically significant. Linear and multivariate regression models will then be used to investigate the strength of associations between preoperative changes in patient body measures (eg, body weight and composition), self-reported outcomes (ie, questionnaire data) and clinical outcomes. Additionally, exploratory analyses comparing outcomes between groups of participants (eg, those that lose weight vs those that do not) will be completed, with groups created using thresholds used in the previous literature^10^ and/or data-driven approaches such as a median split^11^ or optimal cut-point determination^32^.

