Separate linear regression models will be created to investigate the amount of variation in self-reported and clinical outcomes which are explained by preoperative changes in patient body measures. Then, multivariate regression models will be created which combine patient outcome measures that contribute significantly to the estimation of clinical outcomes. Ordinal logistic regression models will also be used to explore the relationship between patient outcome measures and ordinal clinical outcome variables, such as surgical complications (Clavien-Dindo classification) and the surgical approach used. Where the distribution of data indicates it would be appropriate (ie, for non-linear relationships between predictor and outcome variables), other regression approaches such as restricted cubic splines or generalised additive models will be used. Regression analyses are appropriate as this is exploratory research, and this approach allows the observation of relationships between all variables. The regression models will all be adjusted for the variability in time between the assessment points, tumour group and pretreatment therapies where these are shown to reduce residual variance and not introduce collinearity to the model. Any outliers will be investigated to ensure that they are legitimate observations; only implausible data will be removed.

Multiple regression models will be assessed for multicollinearity between input variables using variance inflation factor and tolerance collinearity statistics and for independence of errors using the Durbin-Watson test statistic. If the largest variance inflation factor value is >10, or tolerance values are below 0.2 this could indicate potential issues in the model associated with multicollinearity. Also, if Durbin-Watson values differed significantly from two this would suggest dependence of errors between input variables in the model. Additionally, regression assumptions (eg, homoscedasticity, normally distributed errors) will be checked via diagnostic plots, and transformations of variables will be used if assumptions are not met.

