Data from the Active Together service shows that many patients are unable to attend assessment appointments prior to surgery, often due to short notice of surgery dates. This might lead to missing data at the presurgery assessment point (visit 2). All efforts will be made to make attending appointments as convenient as possible for patients. Additionally, patients are routinely weighed before surgery; therefore, the key outcomes of body mass change and surgical outcomes should always be available. Therefore, statistical analyses for body mass change will include all participants, and analyses including body composition, size and shape, and questionnaire data will be performed on a smaller cohort if some data are missing.

Complete case analyses will be performed when covariates (eg, body composition variables) contain missing data. Complete case analysis can lead to biased parameter estimates in regression models if the data are not missing completely at random (MCAR). Therefore, graphical techniques and Little’s hypothesis test of the MCAR assumption will be used to explore whether the MCAR assumption is a reasonable one to make with the collected data. If not, a standard multiple imputation method will be implemented (eg, Multiple Imputation by Chained Equations, Linear Regression Imputation or Predictive Mean Matching).

For linear regression analyses, assuming a medium effect size (F^2^=0.15), significance level=0.05, power=0.8 and number of predictors=6, a sample size of 98 is required.^33^ For correlation, assuming a two-tailed test, a medium effect size (rho=0.3), significance level=0.05 and power=0.8, a sample size of 84 is required.^33^ Therefore, a sample size of 100 participants is required to detect medium effect sizes with acceptable statistical power. Furthermore, 100 participants is a reasonable estimate of the number of potential participants within the study’s time frame based on the demographics of current and previous Active Together patients (ie, number of patients awaiting surgery for upper GI or colorectal cancer with a BMI ≥30 kg/m^2^).

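### Explained variation reported from the significance-screened combined models will be optimistic, even as adjusted R2, and the separate adjusted models need an incremental R2 to isolate the body-change share

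*Protocol article*

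**What the plan says.** All of this is in the protocol article, under Statistics and analysis. The regression work has two stages.

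- **Separate models.** "Separate linear regression models will be created to investigate the amount of variation in self-reported and clinical outcomes which are explained by preoperative changes" in body measures. No significance screen precedes this stage.
- **Combined models.** "Then, multivariate regression models will be created which combine patient outcome measures that contribute significantly to the estimation of clinical outcomes".

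One adjustment rule covers both stages: "The regression models will all be adjusted for the variability in time between the assessment points, tumour group and pretreatment therapies", with the condition "where these are shown to reduce residual variance and not introduce collinearity to the model". An adjuster therefore stays in partly because it accounts for outcome variation.

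The threshold "P values <0.05 will be considered statistically significant" is given next to the correlations; no other level is stated for the screen. The article names no R2 variant and mentions no internal validation or shrinkage. It describes the research as exploratory. It also expects fewer participants in the composition, size and questionnaire analyses if data are missing.

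**The concern.** Explained variation is the stated purpose of the separate models, so readers will take the reported percentage as the contribution of body change. Two features can make such a percentage too large.

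1. **Adjusters' share.** The R2 of a model holding body change plus tumour group, interval and therapies describes all of them together. Upper GI and colorectal resections are pooled, so tumour group may well account for part of the variation in operating time or stay.
2. **Screening.** A measure enters a combined model because its association looked strong in these data. Refitting on the same data keeps that favourable chance error. Adjusted R2 corrects for the number of terms kept, not for the number tried.

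The second feature biases a reported magnitude. It differs from the false-positive problem, although the same rule causes both.

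**Working it through.** **1. The plan's own figure.** Inputs: "assuming a medium effect size (F^2^=0.15), significance level=0.05, power=0.8 and number of predictors=6, a sample size of 98 is required". Method: noncentral F test with 6 and N-7 degrees of freedom and noncentrality f2 x N. At N=98 the noncentrality is 0.15 x 98 = 14.7 and power is 0.804, so 98 reproduces; at N=100 power is 0.813. The effect size corresponds to R2 = 0.15/1.15 = 0.130.

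This N arises only when all six predictors are tested jointly. With six predictors in the model, testing an increment of 1, 2, 3, 4 or 5 of them needs 55, 68, 77, 85 or 92. The study was therefore sized on a whole-model R2. That is indirect evidence about what might be reported, not proof.

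**2. Adjusters' share (separate models).** Simulation, N=100, 4,000 runs per setting: three adjusters with an assumed joint share, and one independent body-change variable that truly explains nothing.

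| Adjusters' true share (assumed) | Whole-model R2 | Adjusted R2 | Increment in R2 from body change |
|---|---|---|---|
| 5% | 0.087 | 0.048 | 0.010 |
| 10% | 0.135 | 0.098 | 0.009 |
| 20% | 0.231 | 0.198 | 0.008 |
| 30% | 0.323 | 0.294 | 0.007 |

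The increment in adjusted R2 is about 0 throughout. Adjusted R2 of the whole model does not separate the two shares; the increment does.

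**3. Why adjusted R2 does not undo a screen.** A single measure that just reaches p=0.05 at N=100 has R2 = t2/(t2 + 98). With t = 1.984 this is 3.94/101.94 = 0.039. Its adjusted R2 is 1 - (1 - 0.0386) x 99/98 = 0.029. Any measure that passes alone therefore shows at least 2.9% adjusted R2, whatever the truth.

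**4. Screening with no true association (combined models).** K independent candidates (K assumed), screened at p<0.05 and refitted on the same 100 people; 4,000 runs each. The chance that any passes agrees with 1 - 0.95^K (0.265, 0.401, 0.537, 0.642).

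| K | At least one kept | Mean R2 if kept | Mean adjusted R2 if kept |
|---|---|---|---|
| 6 | 0.27 | 0.063 | 0.052 |
| 10 | 0.40 | 0.067 | 0.056 |
| 15 | 0.55 | 0.077 | 0.064 |
| 20 | 0.64 | 0.084 | 0.069 |

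**5. Closer to the plan: adjusters in the screening models.** Assumed: adjusters explain 20%, body measures nothing, 6 to 15 candidates with mutual correlation 0.3. At N=100 about 25-47% of studies keep at least one measure. The kept measures then add 5-6% to R2, or about 4-5% to adjusted R2. At N=70 (an assumed smaller composition cohort) they add 7-8%, or 6-7% adjusted.

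**6. Averaged over all null studies.** Counting 0 where nothing is kept, the adjusted figure at N=100 in step 5 runs from 0.25 x 4% = 1.0% to 0.47 x 5% = 2.4%.

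**7. With a real signal.** If two of the K candidates (6 to 20) carry a true R2 of 0.10 in total, mean adjusted R2 after screening is 0.110-0.130. The variables actually selected carry only 0.065-0.070.

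**The case against.** **The two stages are distinct.** A reader might infer that the percentage attributed to body change is itself taken from screened models. The text does not support that. The sentence on explained variation concerns the separate models, which come before the screen, and the article never says that an R2 will be reported from the combined ones. This stands, so the two parts of the point have to be kept apart.

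**No statistic is named.** A reader might also infer that whole-model R2 will be credited to body change. The wording fits an incremental R2 at least as well, and the choice may sit in an analysis plan that is not shown. The sample-size calculation leans towards whole-model R2 but does not settle it. The adjusters enter only on a condition, so their number in any model is unknown. That a reported share would be mostly tumour group or treatment is likewise not shown. This part is therefore conditional.

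**The work is exploratory, and the null figures are conditional.** The 4-6% applies only when nothing is truly associated and at least one measure passes; step 6 gives the smaller average. That limits the size. It does not remove the bias, because the published combined models will be exactly those in which something passed, and step 7 shows optimism with a real signal too. An exploratory label tempers p-values; it does not correct a magnitude.

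**Overlap.** Optimism and false positives come from the same selection rule and could be dealt with in one edit. That is fair, but it does not remove the need for a corrected R2.

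**Conclusion.** The point holds in a limited form, as a cheap improvement.

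- **Combined models.** The article itself fixes a selection rule that uses the same participants, with no validation stated. Any explained variation reported from these models will be optimistic, also as adjusted R2. Under a complete null with 6 to 15 candidates, about a quarter to a half of studies keep at least one measure and then show about 4-6% adjusted R2 at N=100, against a truth of 0. Smaller composition or questionnaire cohorts make this worse.
- **Separate models.** If whole-model R2 were reported, it would include whatever the retained adjusters explain. Whether it will be is not stated.

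The sizes rest on assumed numbers of candidates, correlations, adjuster shares and (for N=70) cohort size, and on a screening level of 0.05, which the article states only beside the correlations. Other values change the size, not the direction.

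**What to change.** In Statistics and analysis, where the separate and combined models are described:

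1. For the separate models, define explained variation as the increase in R2 when the body-change terms are added to a model holding the adjusters alone, and give it with a bootstrap confidence interval.
2. For the combined models, report an optimism-corrected R2 from a bootstrap that repeats the screening step in every resample, using the analysis set of that model.

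The cost is a few lines of analysis code and a sentence or two of text, with no new data and no change of design. The downside is that the reported R2 values will be smaller.

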### Statistics and analysis

Directed acyclic graphs have been created for the outcome measures in this study to identify confounding factors and determine which variables to adjust for during analysis. Figure 2 shows the causal pathway and potential confounders for investigating the effect of body composition changes on surgical outcomes. Online supplemental material 3 includes directed acyclic graphs for preoperative well-being, post-treatment well-being and 1-year survival. All quantitative data will be treated as continuous data, excluding Clavien-Dindo classification of postoperative surgical complications (ordinal) and the surgical approach, type of surgical complications and treatment pathway (nominal).

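### The multivariable models select terms by significance rather than from the causal graphs, so a probable mediator can enter and change what the body-change coefficient means

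*Protocol article*

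**What the plan says.** All of this is in the Statistics and analysis section of the protocol article unless noted.

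- **Adjustment rule.** Directed acyclic graphs have been drawn to find confounders and to decide what to adjust for. Figure 2 is described as "Directed acyclic graph for investigating the effect of body composition changes on surgical outcomes", and its legend adds that "Baseline and preoperative well-being include nutritional status, psychological well-being and physical fitness". For the rest, "Online supplemental material 3 includes directed acyclic graphs for preoperative well-being, post-treatment well-being and 1-year survival".
- **Correlation step.** Coefficients relate "outcome measures (eg, body weight, size and shape, body composition, body mass change, PG-SGA-SF, EQ-5D-5L, etc) and clinical outcomes". For the threshold, "P values <0.05 will be considered statistically significant".
- **Separate models.** Self-reported and clinical outcomes are each regressed on preoperative changes in body measures.
- **Combined models.** Next, "multivariate regression models will be created which combine patient outcome measures that contribute significantly to the estimation of clinical outcomes".
- **Common covariates.** Time between assessments, tumour group and pretreatment therapies are added where they reduce residual variance without causing collinearity.
- **Timing.** Under Primary data, both questionnaires are completed at visit 1 and again at visit 2, within 2 weeks before surgery.

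**The concern.** The section contains two rules for what goes into a model, and they can choose different terms. A causal graph sorts variables by their place relative to exposure and outcome. A significance test sorts them by how strongly they relate to the outcome. A confounder and a mediator can both pass that test, and a needed confounder can fail it.

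Preoperative well-being is where this matters. The plan gives it a graph of its own as an outcome, and the separate models treat self-reported measures as explained by body change. It is therefore probably downstream of body change. It may also predict complications or length of stay, which is what would bring it into a combined model. Once it is in, the body-change coefficient excludes whatever acts through nutrition, mood or fitness.

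At stake is interpretation. The Introduction argues that fat loss and muscle loss may have different consequences. If the covariates beside body change differ between outcomes according to p-values, the coefficients cannot be compared across outcomes, and a small one in a combined model is easily misread.

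**Working it through.** **Step 1: the plan's own figures.** The sample size is not in question, but it supplies n and the effect size.

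- Regression: overall F test with f²=0.15, 6 predictors, alpha 0.05 and non-centrality f²×N. The smallest N with power of at least 0.80 is 98 (power 0.804), as stated. At N=100, power is 0.813.
- Correlation: ((1.960+0.842)/atanh(0.3))²+3 = 84.9, so 85 against the stated 84, a trivial difference.

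**Step 2: the text side by side.**

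| Question | What the text supports |
|---|---|
| Are well-being scores eligible for the combined models? | The correlation step lists PG-SGA-SF and EQ-5D-5L beside body mass change as measures set against clinical outcomes. The combined models draw on patient outcome measures. Eligibility is the natural reading. |
| From which visit? | None is named, and both questionnaires are completed at both visits. |
| Is preoperative well-being downstream of body change? | Probably: it has its own graph as an outcome, and self-reported outcomes are regressed on body change. The arrows of Figure 2 are not available here. |
| Does the combination rule refer back to the graphs? | No. |

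**Step 3: effect on the coefficient.** Let X be body change, M preoperative well-being and Y a clinical outcome, all standardised and linear. Let a be the path from X to M, b the path from M to Y, and c the direct path.

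- Without M, the X coefficient estimates the total, c + ab.
- With M, it estimates c = total − ab.

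Inputs: the total of 0.30 is the plan's medium rho; n=100 is the planned size; entry of M at p<0.05 applies the plan's general threshold to the combination step. Paths a and b are **assumptions**, as the documents give no values. Each setting was simulated 4,000 times, and M entered when significant in its own model of Y.

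| a / b | Direct effect (0.30 − ab) | M enters | Mean coefficient under the rule | Power without M | Power under the rule |
|---|---|---|---|---|---|
| 0.2 / 0.2 | 0.26 | 73% | 0.27 | 0.86 | 0.77 |
| 0.3 / 0.3 | 0.21 | 96% | 0.21 | 0.87 | 0.59 |
| 0.5 / 0.4 | 0.10 | 99.8% | 0.10 | 0.86 | 0.16 |

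The loss runs from about 12% (0.265 before rounding, against 0.30) to about 67% (0.10 against 0.30).

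**Step 4: hand check of the last row.** Residual variance is 1 − (0.10² + 0.40² + 2×0.10×0.40×0.5) = 1 − 0.21 = 0.79. The standard error is √(0.79/(100×(1 − 0.5²))) = √(0.79/75) ≈ 0.103. The ratio 0.10/0.103 ≈ 0.97, against a critical value of 1.984, gives power of about 0.16, as simulated.

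**The case against.** The strongest reply has five parts.

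- **The graphs may already deal with it.** If Figure 2 draws preoperative well-being as a mediator, the adjustment rule would exclude it. That is possible, but the combination rule does not say that it yields to the graphs. The conflict in wording stands.
- **The combined models may concern body measures only.** The sentence just before has body change as its only predictor, so the next one could mean combining the body measures that proved significant. This reading is available, though less natural given the list in the correlation step. A reader might infer that the plan definitely places visit 2 well-being beside body change. The text does not say so; it only permits it.
- **The total association is still reported.** This stands. A reader might infer that a real effect acting through nutrition or fitness would be reported as no association. That does not follow, because neither the correlations nor the separate models are described as including preoperative well-being.
- **Direction is uncertain.** Visit 2 scores are taken at the same time as the final body measurements. Worsening nutrition or well-being between visits, including during neo-adjuvant treatment, could drive weight loss as well as follow from it. This stands too, and it argues for reporting both models with clear labels rather than discarding one.
- **The study is exploratory, disclaims causal inference, and is described in a condensed article.** True, but the plan uses causal graphs to choose adjustment and speaks of an effect. Even a purely associational coefficient needs a stable meaning. The point is also not an omission: the article states a selection rule that sits badly with its other rule.

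**Conclusion.** The point holds as a conflict between two stated rules. The graphs are meant to decide adjustment, but significance decides what is combined, with no restriction to baseline scores. The rule can therefore admit a probable mediator, and the body-change coefficient may be total for one outcome and partial for another.

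The size is illustrative. The 12% to 67% loss rests on linear standardised variables, same-sign paths, a total effect of 0.30 and path values that do not come from the documents. Opposite-sign paths would distort the coefficient rather than shrink it. The mediator role is inferred from the Figure 2 legend, the separate graph and the separate models, not seen in the figure. Adjusting for baseline well-being is not the problem. The consequence is confined to the combined models.

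**What to change.** For models of body change on surgical outcomes and survival:

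1. Take the adjustment set for each outcome from its graph and state it in advance. Do not let p-values decide which terms stay.
2. Adjust for baseline (visit 1) well-being where the graph marks it as a confounder.
3. Report the model without preoperative well-being as the main one.
4. Report a model that adds preoperative well-being as a secondary analysis, labelled as a direct association or as prediction. Note that visit 2 scores are concurrent with the final body measurements and may also drive body change.
5. Say which visit's scores are eligible wherever questionnaire or fitness measures are used as predictors.

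This is a change of wording and needs no new data. If Figure 2 already shows preoperative well-being as a mediator, it simply brings the model-building text into line with the figure. The downside is one extra model per outcome.

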#### Secondary data

In addition to the outcomes detailed above that will be gathered by the research team, data will be collected as part of the participants’ usual care from two other sources: from their NHS records for surgical information, hospital length of stay, readmissions and 1-year survival, and from the Active Together service for physical fitness and questionnaire assessments (table 1). These outcomes will be measured at the time points outlined in figure 1. The physical fitness outcomes from Active Together will be collected by members of the Active Together team, with the procedures used to collect this data provided in online supplemental material 2.

**Table 1 T1:** Data collected by the hospital and Active Together.

Hospital data	Active Together outcomes	
Surgical outcomes	Physical fitness	Questionnaires
Clavien-Dindo classification of postoperative surgical complications	6-minute walk test distance (m)	Patient-Generated Subjective Global Assessment Short Form
Type of surgical complications	60-second sit-to-stand repetitions	Quality of life: EuroQol 5-Dimensions 5-Levels
Length of operation time	2-minute step test repetitions	Fatigue: Functional Assessment of Chronic Illness Therapy-Fatigue
Surgical approach	Handgrip strength (kg)	Anxiety: General Anxiety Disorder 7
Length of critical care stay post-surgery	Blood pressure (mm Hg)	Depression: Patient Health Questionnaire 9
Length of hospital stay post-surgery	Physical activity level (exercise vital signs)	Self-Efficacy for Exercise Scale
Readmissions within 30 and 90 days (and reason for this)		
1-year survival		
Treatment pathway		

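### Surgical approach is declared nominal but analysed as ordinal with no stated order, and the rule on continuous data literally takes in 1-year survival and readmissions

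*Protocol article*

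**What the plan says.** All references are to the protocol article.

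- **Data types** (Statistics and analysis, opening paragraph). The default is "All quantitative data will be treated as continuous data, excluding Clavien-Dindo classification of postoperative surgical complications (ordinal". The remaining exceptions are "the surgical approach, type of surgical complications and treatment pathway (nominal". That makes four exceptions: one ordinal and three nominal.
- **Ordinal model** (same section, the paragraph on separate regression models). Ordinal logistic regression is to be used for "ordinal clinical outcome variables, such as surgical complications (Clavien-Dindo classification) and the surgical approach used".
- **Correlation step** (same section, after Figure 2). Pearson or Spearman coefficients relate patient measures to "clinical outcomes (eg, surgical complications, length of stay, number of emergency readmissions and length of operating time". Linear regression follows.
- **Regression step.** Separate linear models are planned for self-reported and clinical outcomes. Splines and generalised additive models are offered where the relationship between predictor and outcome is not linear.
- **Outcomes collected** (Secondary data and Table 1). Data come "from their NHS records for surgical information, hospital length of stay, readmissions and 1-year survival". Table 1 lists "Readmissions within 30 and 90 days (and reason for this". The abstract names operative approach, readmissions and 1-year survival among the surgical outcomes.
- **Survival is meant to be analysed.** The supplement is said to hold "directed acyclic graphs for preoperative well-being, post-treatment well-being and 1-year survival".

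**The concern.** There are two problems of unequal strength.

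The first is a contradiction. A variable cannot be unordered in the typing rule and ordered in the model. A proportional-odds model needs a ranking and returns one odds ratio for moving up it. If the categories have no natural rank, the analyst's coding settles the sign and size of that odds ratio. A listed surgical outcome then has no coherent analysis.

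The second concerns the typing rule. Three of its four exceptions are nominal, so the word quantitative is not being used there to set categorical items aside in advance. 1-year survival (alive or dead) and readmissions (yes/no, or a count that is mostly 0 or 1) are missing from the list. Read literally, they fall under the continuous default and so go on to linear regression. For a binary outcome, that model can give fitted probabilities outside 0 to 1, and its usual standard errors assume a constant variance that the outcome does not have.

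**Working it through.** **1. The plan's own figures.** These are not in dispute, but they show what the design covers.
- Regression: overall F test, noncentrality 0.15 × N, 6 and N − 7 degrees of freedom, alpha 0.05. The smallest N with power 0.80 is 98 (power 0.804), and power at 100 is 0.813. This matches the stated 98.
- Correlation: N = ((1.960 + 0.842) / atanh 0.3)² + 3 = 84.9, so 85. A noncentral-t version gives 82. The stated 84 lies between them.

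Both calculations apply to linear regression and correlation only. Neither covers a nominal, binary or survival outcome.

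**2. Surgical approach, statements side by side.**

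| Place in Statistics and analysis | Status of surgical approach |
|---|---|
| Opening paragraph | Nominal |
| Paragraph on separate regression models | Ordinal outcome, ordinal logistic regression |

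No order of categories is stated, and no multinomial or binary logistic model is named.

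**3. What the coding does.** This is an illustration on assumed data: 100 participants, three categories A, B and C, and an exposure that raises the odds of B only. The sizes below correspond to an odds ratio for B of roughly 2 per standard deviation with the categories about equally common.

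| Order imposed | Median ordinal odds ratio per SD |
|---|---|
| A < B < C | 1.01 |
| A < C < B | 1.75 |
| B < A < C | 0.57 |

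The second and third values are close to reciprocals (1/1.75 = 0.57). The same association appears as null, positive or negative. The exact values depend on the assumed strength, but the dependence on coding does not.

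**4. Survival and readmissions.** Each was traced through the rules.
- *1-year survival*: collected, has its own directed acyclic graph, is not an exception, and is not among the examples at the correlation step. Only the default rule and the general phrase clinical outcomes place it under a linear model.
- *Readmissions*: collected within two windows, not an exception, and named explicitly as a number at the correlation step. Spearman is tolerable there. The regression step that follows is linear.

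**5. Information in a binary outcome at N = 100.** The documents give no event rate, so a range is assumed. For logistic regression on one standardised predictor, the smallest odds ratio per SD detectable with 80% power is exp[(1.960 + 0.842) / √(100 × p × (1 − p))].

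| Assumed event rate p | Events | Detectable odds ratio per SD |
|---|---|---|
| 5% | 5 | 3.6 |
| 10% | 10 | 2.5 |
| 20% | 20 | 2.0 |
| 30% | 30 | 1.8 |

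If events are few, a correctly typed model will support few adjustment terms.

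**The case against.** Several counter-arguments carry weight.

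- **Surgical approach may be harmless in practice.** Table 1 does not list its levels. With two levels, ordinal and binary logistic regression are the same model and order is irrelevant. With levels ranked by invasiveness, an ordinal model could be defended. Both points stand, but they require the document to state the levels or the order and to stop calling the variable nominal.
- **A reader might infer that the plan fits 1-year survival by linear regression.** No sentence says so. The inference rests on a loosely worded default, and the article condenses a fuller protocol, so not naming a model for every outcome is not in itself a fault. What stands is narrower: the article does state a typing rule, and as worded it misplaces this outcome.
- **A reader might say that readmissions are sent to Pearson correlation.** The text describes a count and allows Spearman, so the correlation step can be acceptable. Only the linear regression step is unsuitable.
- **A reader might divide the expected deaths by six predictors.** The six belong to the sample size for linear regression. No six-predictor survival model is proposed, so that ratio describes nothing in the plan.
- **Safeguards exist.** Residual plots and transformations are planned, and generalised additive models are allowed. Transformation may help a count but cannot repair a 0/1 outcome. The additive models are triggered by the shape of a relationship, not by the type of outcome.
- **The study is exploratory.** This lowers the stakes, but it does not reconcile the two statements on surgical approach.

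**Conclusion.** The contradiction on surgical approach is certain from the text and should be resolved before outcome data are seen. It affects one listed surgical outcome. Its practical size depends on the number of levels, which is not given: none with two levels, and possibly a change in the sign of the association with three or more unordered ones.

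The point on survival and readmissions holds in a smaller form. The literal typing rule covers outcomes for which linear regression is unsuitable, and the list of exceptions needs amending. The documents do not show that a linear survival model is intended. The loss from few events cannot be sized from the documents, and the table of event rates is an assumed range only. The stated sample sizes of 98 and 84 are not in error.

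**What to change.** 1. **Surgical approach.** Reconcile the two statements. Keep ordinal logistic regression for the Clavien-Dindo classification. Model surgical approach with multinomial logistic regression, or binary logistic regression if there are two categories. Alternatively, declare it ordinal in the opening paragraph and state and justify the order.
2. **Exceptions to the continuous rule.** Add 1-year survival and readmissions within 30 and 90 days, and state the type of each.
3. **Matching models.** Use binary logistic regression or a count model for readmissions, according to whether they are recorded as yes/no or as a number. Use logistic regression for 1-year survival, or a time-to-event model if dates of death are collected.
4. **Adjustment.** State that the number of adjustment terms for these outcomes will be kept in line with the observed number of events.

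The cost is a few sentences and slightly more analysis work. No further data collection is needed, and no sample size changes. With few events, less adjustment can be claimed for survival and readmissions than for the continuous outcomes.
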